### **Consent for publication**

Not applicable.

### **Availability of data and materials**

The datasets during and/or analysed during the current study will be made available from the corresponding author on reasonable request

### **Competing interests**

The authors declare that they have no competing interests

### **Funding**

The study is being funded by a four-year Medical Research Futures Fund (MRFF – Australian Federal Government) grant. The funding was not provided with any conditions and the MRFF has no authority over the design of the study or collection, management, analysis or interpretation of data or the writing of manuscripts for submission. No industry funding or other sources of funding are being used for this trial.

### **Authors' contributions**

All authors listed have contributed to this protocol and the ICMJE guidelines were consulted for determining authorship. VS, IAH, RB, SG, SA, JMN, RdS, NP, INA, ML, DB, KC and TLK were responsible for the planning of the trial, protocol development and writing, TLK and

NP were responsible for the description of the statistical analyses used. All authors reviewed the final version of this manuscript prior to submission.

### **Acknowledgements**

Not applicable.

## **ABSTRACT**

### **Background:**

This *a priori* statistical analysis plan describes the analysis for CRISTAL.

### **Methods:**

CRISTAL (cluster-randomised, crossover, non-inferiority trial of aspirin compared to low molecular weight heparin for venous thromboembolism prophylaxis in hip or knee arthroplasty, a registry nested study) aims to determine whether aspirin is non-inferior to low molecular weight heparin (LMWH) in preventing symptomatic venous thromboembolism (VTE) following hip arthroplasty (HA) or knee arthroplasty (KA). The study is nested within the Australian Orthopaedic Association National Joint Replacement Registry. The trial was commenced in April 2019 and after an unplanned interim analysis, recruitment was stopped (December 2020), as the stopping rule was met for the primary outcome.

The clusters comprised hospitals performing > 250 HA and/or KA procedures per annum, whereby all adults (> 18 years) undergoing HA or KA were recruited. Each hospital was randomised to commence with aspirin, orally, 85-150mg daily or LMWH (enoxaparin), 40mg, subcutaneously, daily within 24 hours postoperatively, for 35 days after HA and 14 days after KA. Crossover was planned once the registration target was met for the first arm.

The primary end point is symptomatic VTE within 90 days. Secondary outcomes include readmission, reoperation, major bleeding and death within 90 days, and reoperation and patient-reported pain, function and health status at 6 months.

The main analyses will focus on the primary and secondary outcomes for patients undergoing elective primary total HA and KA for osteoarthritis. The analysis will use an intention-to-treat approach with cluster summary methods to compare treatment arms. As the trial stopped early, analyses will account for incomplete cluster crossover and unequal cluster sizes.

### **Conclusions:**

This paper provides a detailed statistical analysis plan for CRISTAL.

**Trial registration:** Australian and New Zealand Clinical Trials Registry, ID: ACTRN12618001879257. Registered on 19/11/2018.

### **Key Words**

Venous Thromboembolism, Hip Arthroplasty, Knee Arthroplasty, Aspirin, Low Molecular Weight Heparin, Statistical Analysis Plan

## **MANUSCRIPT**

### **Background**

Despite the increasing use of aspirin as a sole chemotherapeutic agent for symptomatic venous thromboembolic event (VTE) prophylaxis following hip arthroplasty (HA) and knee arthroplasty (KA) [1], there remains limited high quality comparative evidence for its safety and efficacy. The majority of studies supporting the safety and efficacy of aspirin compared to other agents, including low molecular weight heparin (LMWH), have been retrospective or non-randomised [2-11]. The only randomised trials have been underpowered or have used an alternative form of prophylaxis (e.g., LMWH or a novel oral anticoagulant (NOAC)) for the immediate postoperative period following HA or KA prior to changing to aspirin for extended prophylaxis, which does not reflect the way aspirin is used in Australia [12, 13]. CRISTAL is a pragmatic, multicentre cluster-randomised, two period cross-sectional crossover trial that aims to determine if aspirin is non-inferior to LMWH in the prevention of symptomatic VTE following HA and KA. It is nested within the Australian Orthopaedic Association National Joint Replacement Registry (AOANJRR).

The trial commenced in April 2019 and the estimated timeline for completion of patient registration was 24 months. However, after an unplanned interim analysis in which the trial stopping rule was met, patient registration was ceased in December 2020, resulting in incomplete crossover. This statistical analysis plan details the planned analyses for CRISTAL to facilitate transparency of data analysis. The CONSORT statement for cluster randomised trials was referred to in preparation of this document [14]. The trial protocol has previously been published [15].

### **STUDY OVERVIEW**

#### **Ethics**

Ethics approval was granted from all relevant central, lead ethics committees involved and all participating hospitals, as outlined in the published trial protocol [15]. The trial is registered with the Australian New Zealand Clinical Trials Registry (ACTRN12618001879257p) and is endorsed by the Australia and New Zealand Musculoskeletal (ANZMUSC) Clinical Trials Network.

#### **Participating Hospitals and Patient Registration**

The clusters in CRISTAL were defined as hospitals where hip and knee arthroplasty procedures were performed. Hospitals were eligible for recruitment provided they agreed to follow the trial protocol and if they performed greater than 250 HA and/or KA procedures per annum. There were 31 hospitals (clusters) that were recruited.

Each recruited hospital was responsible for registering patients and complying with the trial protocol. The AOANJRR routinely collects data pertaining to the procedure, patient age, sex, American Society of Anaesthesiologists (ASA) class and body mass index (BMI) and death on all patients undergoing HA and KA procedures. Patient-reported outcomes are collected through the electronic Clinical Trials Platform, which requires pre-operative registration of the patient onto the electronic system. All adult (age 18 and older) patients undergoing HA or KA were eligible for registration into the study and eligible to receive the allocated study drug, except for those who were already on long-term anticoagulation (specifically a NOAC,

warfarin or dual antiplatelet therapy (DAPT)) and those with a medical contraindication to either drug, e.g., an allergy or a medical comorbidity such as thrombophilia that precluded treatment with the study drug.

Patients who were not registered in the electronic Clinical Trials Platform will be included in secondary analyses, as procedure information, demographics and mortality were still recorded even though the primary outcome and other patient-reported outcomes were not recorded.

### **Intervention**

Each hospital (cluster) was allocated to consecutive periods of a standard protocol of LMWH and a standard protocol of aspirin as VTE prophylaxis, with the order being randomised. Patients in the aspirin group received aspirin at 85-150mg once daily, orally for 35 days post HA and for 14 days post KA, commencing within 24 hours of surgery. Patients in the LMWH group received enoxaparin at 40mg once daily, subcutaneously for the same time periods, with this dose reduced to 20mg for patients who weigh less than 50kg and for patients with an estimated glomerular filtration rate (eGFR) of less than 30mL/min who are not on dialysis. Other interventions that were standard across all sites were the intra- and post-operative use of intermittent pneumatic compression (IPC) calf devices until patients are mobile, the use of compression stockings, and mobilisation offered on day 0 or day 1 postoperatively.

### **Randomisation and allocation**

Study investigators have remained blinded to group allocation. All 31 participating hospitals were randomised to commence with either LMWH or aspirin, in randomly permuted blocks of size four by statisticians from the South Australian Health and Medical Research Institute (SAHMRI), independent of study investigators. The randomisation sequence was generated using an online application [16] and this was provided to an unblinded data manager from SAHMRI. The hospital was then allocated to a treatment sequence by SAHMRI staff and this information was provided to the AOANJRR (independent of study investigators), with the site being informed of their allocated treatment arm the week prior to commencing initial patient registration. Hospitals followed the designed protocol for patients for their allocated treatment arm and were advised to crossover to the alternate treatment once the sample size for the first treatment arm was met.

For clusters who did not reach the sample size for the first arm within 18 months of commencement, crossover occurred prior to reaching the sample size so that an equal number of patients could be registered in each arm within the study timeframe.

### **Evaluation of adherence to the study protocol and protocol deviations**

At a hospital level, during the course of the trial each hospital was audited within the first month of each treatment arm to ensure they were complying with the trial protocol and to ensure each cluster received the intended allocated treatment. The audit consisted of the first 20 patients of each treatment arm. If a site had a compliance of less than 80%, the site was educated on methods of improving protocol compliance and subsequently re-audited until compliance to the protocol was above 80%.

Hospitals were also advised to inform trial co-ordinators of patients not receiving the correct study drug or those patients who had the study drug withheld for greater than 48 hours due to side effects (e.g. allergy, excessive wound drainage or bleeding events). These protocol deviations were recorded using the Clinical Trials Platform.

### **Outcome variables**

The primary outcome of the study is symptomatic VTE within 90 days of surgery. Secondary outcomes are:

- Deep vein thrombosis (DVT) only (total, below-knee and above-knee) within 90 days
- Pulmonary embolism (PE) only within 90 days
- Readmission related to the original surgery or associated treatment (including bleeding and VTE-related) within 90 days
- Reoperation on the same joint within 90 days and within 6 months of surgery
- Major bleeding events within 90 days defined as bleeding events resulting in readmission, reoperation or death
- Death within 90 days
- Change in patient-reported pain, function and health status measures as measured by the Oxford Hip Score (OHS), Oxford Knee Score (OKS), EQ-5D score and the EQ-VAS from baseline to 6 months postoperatively

Outcome and demographic data were collected preoperatively (demographics, patient reported pain, function and health status) and at 90 days and 6 months postoperatively. Data for all primary and secondary outcomes are patient-reported (except for death). All patients who responded 'yes' to having experienced a VTE or a secondary operation within 6 months had this result verified by AOANJRR staff through contact with treating doctors and hospitals. A random audit of 200 patients who did not report a VTE event was undertaken to detect the false negative reporting rate. All data collected for registered patients specific to CRISTAL have been outlined in the published protocol [15]. Mortality data were collected through linkage between the AOANJRR and the National Death Index.

In the published protocol [15], mortality was to be measured at 90 days and 6 months. Due to the lack of sensitivity in measuring VTE-related mortality at 6 months, and due to the lag in data availability for mortality, we will only analyse mortality at 90 days [17].

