The Australian Orthopaedic Association National Joint Replacement Registry (AOANJRR) was established in 1999 and reports on revision surgery and mortality after joint arthroplasty in Australia, with close to complete national coverage. The AOANJRR has established a system to directly capture data entered by patients pre- and post-operatively; this system is a platform for the conduct of clinical trials and is incorporated as part of the AOANJRR (not a standalone project). The proposed CRISTAL trial will be embedded within the Clinical Trials Platform of the AOANJRR.

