#### **3.3. Intervention**

Each site will be allocated to two consecutive periods of a standard protocol of aspirin and a standard protocol of LMWH for VTE prophylaxis with the order of the two periods determined by randomisation at a 1:1 ratio, on an open label basis.

Each site will adhere to the initially randomised protocol for a time period based on surgical volume aiming for 250 patients eligible for the primary analysis per group. The target

recruitment time period for each group will be 12 months, but may extend beyond this if required. Total recruitment (all arthroplasties) to each group is expected to be 300 patients. Patients will be informed of the trial during initial data entry. Patients will be specifically asked at the time of study entry for consent for follow-up, for use of their data in research, and use of linked data to measure and verify surgical outcomes (Appendix 1). Patients will not be individually consenting to be randomised to either aspirin or LMWH, as both drugs represent standard practice and randomisation is not at the patient level. Further details on the consent process is listed in protocol (section 4.3).

Patients will be followed up at 90 (90-120) days and 6 (5-7) months, electronically, with telephone back up. To ensure minimal inconvenience a maximum of three successful reminders will be sent to the patient to complete their follow-up CRISTAL questions. Patients will be contacted beyond 100 days and 6.5 months via telephone, if surveys remain incomplete and if initial telephone contact has not been successful.

- 1st reminder
  - Pre-operative - 2 days after registration
  - 90-day post-operative – 90 days post operation
  - 6-months post-operative - 5 months + 2 weeks post operation
- 2nd reminder
  - Pre-operative - 3 days after the first reminder
  - 90-day post-operative – 95 days post-operation
  - 6-months post-operative – 2 weeks after first reminder
- 3rd reminder
  - Pre-operative - 4 days after the second reminder,
  - 90-day post-operative – 100 days after operation
  - 6-months post-operative – 2 weeks after second reminder

The electronic system used for data collection is also equipped with a Save and Complete feature which will allow an incomplete set of questions to be completed by the patient at a later date.

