### **3.17. Auditing and Data validation**

Positive outcomes (reported VTE) reported by patients will be confirmed by contacting hospitals or treating doctors. These will be adjudicated by the Outcome Verification Committee.

A sample of negative outcomes (patients reporting the absence of VTE) will be verified in a similar manner in a random sample of 200 patients with negative outcomes. Complications will be adjudicated by the Outcome Verification Committee. ANZMUSC will audit the study.

The AOANJRR Data Linkage project will be used to test the accuracy of outcome reporting (readmission, re-operation, drug prescriptions). The AOANJRR also links to the National Death Index (NDI) twice a year (February and September). If a patient, who has participated in the CRISTAL project, is flagged as deceased in the AOANJRR database this can also be transferred to the CRISTAL system and no further contact will be made, reducing distress for families.

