### Consent to AOANJRR Clinical Trials Platform

Consent will be obtained electronically. All data collection for this project is electronic. This provides efficiency and effectiveness (less error) and allows a better way to impart information relevant to the consent process. The participant information and consent form will be displayed on the screen. It contains all elements required for a consent form (see Appendix 1). The information under each statement will be expandable. Patients will be provided the option to 'agree to the statement' or 'learn more'. If the patient agrees they will be navigated to the next statement. If the patient chooses to learn more the additional information will be displayed. Once all statements have been agreed to the patient will be

able to choose whether they give consent or no longer wish to participate in the study. If the patient consents to participate they will be directed to the next page where they can complete the required pre-operative CRISTAL questions relevant to their procedure. If the patient chooses not to consent after the initial registration, then all personal information collected at registration will be deleted from the database. The only data that will be retained is:

- Hospital Name (if available)
- Surgeon Name (if available)
- Date of registration

If the patient elects to withdraw at the time of their post-operative assessment, then no further follow-up will be undertaken.

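### Reoperation is known only for patients who answer the survey; the host registry's own revision records, which do not depend on response, have no role in the SAP

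*Supplement*

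**What the plan says.** **Source of the outcome.** The final SAP, Outcome variables, lists reoperation on the same joint within 90 days and within 6 months as a secondary outcome, and says: "Data for all primary and secondary outcomes are patient-reported (except for death". Mortality comes from linkage with the National Death Index.

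**Verification.** The same section says: "All patients who responded 'yes' to having experienced a VTE or a secondary operation within 6 months had this result verified by AOANJRR staff", through treating doctors and hospitals. For negative answers it describes one audit: "A random audit of 200 patients who did not report a VTE event was undertaken to detect the false negative reporting rate". That audit concerns VTE.

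**Missing data.** Under Methods for handling missing data, the final SAP plans multiple imputation by chained equations and assumes missing at random. It abandons that imputation if perfect prediction of a rare outcome could cause bias. Inverse probability weighting is confined to the primary outcome.

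**What the registry holds.** Final protocol 2.1 says the host registry "was established in 1999 and reports on revision surgery and mortality after joint arthroplasty in Australia, with close to complete national coverage". The final SAP, Participating Hospitals and Patient Registration, adds that procedure data are collected routinely on all hip and knee arthroplasty patients, and that procedure, demographic and mortality data exist for unregistered patients too.

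**Consent and linkage.** Final protocol 3.3 seeks consent for "use of linked data to measure and verify surgical outcomes". Final protocol 3.17 says: "The AOANJRR Data Linkage project will be used to test the accuracy of outcome reporting (readmission, re-operation, drug prescriptions").

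**The concern.** Reoperation is a safety outcome in a comparison of two antithrombotic drugs, and it also enters the SAP's definition of major bleeding. As planned, its ascertainment depends on who answers a questionnaire. A further operation may make a patient more or less likely to respond. The stated ground for missing at random, that loss mostly reflects difficulty in contacting people, is not tested for this outcome.

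The SAP already accepts registry-based follow-up for death. It analyses mortality in population 5, registered or not, to assess the effect of the protocol at hospital level, which is the unit of randomisation. The same reasoning applies to revision surgery, which the host registry also records regardless of response. If linkage shows a revision in a patient who answered no or did not answer, no rule says what happens to that event.

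**Working it through.** **1. Routes by which a reoperation can be counted under the final SAP**

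| Patient | Route to the reoperation outcome |
|---|---|
| Answers yes | Counted after verification with doctors or hospital |
| Answers no, but was revised | None in the SAP; the protocol 3.17 linkage might reveal it, with no stated consequence |
| Does not answer | Imputed under missing at random; if imputation is abandoned, no fallback for reoperation is named |
| Not registered | None; outside mortality, this patient enters no outcome analysis |

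The registry could inform the last three rows for revision surgery. The SAP's own population definitions treat revision as a form of hip or knee arthroplasty. A population 1 patient revised at a participating hospital during the study would therefore also appear in population 5 as a revision procedure, without necessarily counting as a reoperation.

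**2. The plan's own figures.** The documents give no reoperation rate and no sample size for this outcome. The registration target reproduces: 251 × 2 × 31 = 15,562. With 27% removed, 15,562 × 0.73 = 11,360, which covers the 11,160 required. The final SAP describes 27% as a maximum that also absorbs other uncertainties, and expects actual loss to be lower. Recruitment stopped early, so 15,562 was a target.

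**3. Illustration (assumed inputs).** Reoperations among non-responders = registered × loss × rate, with equal rates in responders and non-responders. Loss of 5–27% and a 6-month rate of 1–3% are assumptions; only the 27% ceiling comes from the documents.

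- Per 1,000 registered: 1,000 × 0.05 × 0.01 = 0.5, up to 1,000 × 0.27 × 0.03 = 8.1.
- At the full target: 15,562 × 0.05 × 0.01 = 8, up to 15,562 × 0.27 × 0.03 = 126. The early stop makes the actual number smaller at any given loss and rate.
- If half of these are revisions (assumed), the registry would recover about 4 to 63 at the full target.

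**4. Effect on the reported rate if missing at random fails (assumed inputs).** Take 2% in responders and 4% in non-responders.

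- 10% loss: true rate 0.90 × 2% + 0.10 × 4% = 2.2%; complete cases show 2.0%, too low by 0.2 points.
- 27% loss: 0.73 × 2% + 0.27 × 4% = 2.54%; too low by 0.54 points.

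These are errors in the level. If the pattern is the same in both arms and the arms do not truly differ, the risk difference stays at zero.

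**5. Why the two sources should not be merged for non-responders.** Suppose a registry revision counts as a reoperation when the survey is missing, while non-responders without a revision stay missing. With an assumed 1.5% risk that is all revision, at the full target and 27% loss:

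- responders contribute 11,360 × 0.015 = 170 events;
- non-responders number 15,562 − 11,360 = 4,202 and contribute 4,202 × 0.015 = 63 events.

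The merged rate is (170 + 63)/(11,360 + 63) = 233/11,423 = 2.0%, against a true 1.5%. Events enter and non-events do not. Counting the remaining non-responders as negative would instead misclassify any non-revision reoperations among them.

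**The case against.** The case against has real weight.

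- **The registry is not ignored.** A reader might infer that negative reoperation reports go unchecked. Final protocol 3.17 contradicts that: linkage tests the accuracy of reoperation reporting, and such a test is not limited to yes answers. What remains is that the SAP gives the result no role.
- **Reoperation is wider than revision.** Final protocol 3.7 includes manipulation under anaesthesia, reduction of dislocation and wound repair. Near-complete coverage is documented for revision and mortality only. It would be wrong to say the registry holds every reoperation in non-responders; it holds a subset of unknown size.
- **Reported events are verified**, telephone back-up limits loss, and imputation is planned where feasible. This stands, but none of it observes the outcome in non-responders.
- **No bias between arms is shown.** Final protocol 3.12 says patients are not told whether they are in the intervention or control group, and that telephone assessors are blinded. The documents give no ground for assuming that response differs by drug.
- **Withdrawal.** Final protocol 4.3 says: "If the patient elects to withdraw at the time of their post-operative assessment, then no further follow-up will be undertaken". A reader might take this to end all use of registry data. The text does not say so, nor does it say that such data are discarded. Recruitment ended in December 2020, before the final SAP of 20 July 2021, so rewording consent text could not alter what patients had agreed to.

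**Conclusion.** The point holds as a gap in ascertainment and in specification for one secondary safety outcome. Reoperation depends on survey response, the SAP has no sensitivity analysis of missingness for it, and a response-independent record of its revision component is already held by the host registry but unused in the SAP.

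The gain in events cannot be computed from the documents; the ranges above rest on assumed rates, loss and revision share. Neither a treatment-related bias nor a large loss of events can be claimed. The VTE result and the non-inferiority conclusion are unaffected. The change is worth making because it is cheap and removes dependence on response for part of a safety outcome.

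**What to change.** Add to the final SAP, as a separate secondary outcome or a sensitivity analysis:

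- registry-recorded revision of the index joint within 90 days and within 6 months of surgery, for populations 1 to 5, with all patients in the denominator whether or not they answered the survey;
- analysis by the same composite cluster-summary method as the other outcomes, with absolute risk difference and 95% confidence interval;
- presentation beside the verified patient-reported reoperation outcome, without merging the two for non-responders;
- a short report of agreement between patient report and registry record from the protocol 3.17 linkage.

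No change to the withdrawal text is needed for this.

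Cost: one query of data the registry already holds, a row in the outcome tables (with population 5 reported alongside its mortality analysis) and a few sentences in the SAP. Downside: the new outcome captures only reoperations recorded as revisions, which is why the patient-reported outcome stays.
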